^. While it remains unclear to what extent suboptimal drug exposures directly contribute to these resistance patterns, previous studies have reported inadequate antibiotic concentrations to drive development of AMR
^
10
^. Other drivers of AMR include genetic mechanisms which also play a significant role in the emergence and spread of resistance to antimicrobials
^
15
^.

Despite the potential contribution of inadequate drug exposure to AMR, the pharmacokinetic (PK) profiles of commonly prescribed antibiotics in PLWH are not well characterized. Ceftriaxone and amoxicillin may not exhibit significant DDI with ART but some ARVs like ritonavir-boosted protease inhibitors can inhibit transporters like p-glycoprotein and multi-drug resistance protein 2, potentially increasing azithromycin exposure and raising the risk of arrythmias
^
16
^. However, no clinical PK studies have been conducted to investigate these potential interactions, and dose adjustments are not currently recommended.

Therapeutic drug monitoring (TDM) uses plasma drug concentrations to assess whether a given dose achieves optimal drug exposure
^
17
^. It helps evaluate attainment of PK targets for the antibiotics and provides objective data to guide dosing decisions. These PK targets are often based on drug exposure parameters like the area under the concentration-time curve (AUC) or peak/trough concentrations relative to the minimum inhibitory concentration (MIC) of the pathogen. For example, azithromycin and ciprofloxacin require AUC/MIC ratios of ≥5
^
18
^ and ≥125
^
19
^, respectively, while ceftriaxone has a minimum threshold of 8 mg/L
^20^. Amoxicillin efficacy depends on maintaining concentrations above the MIC for at least 40% of the dosing interval
^
21
^. However, MIC testing is rarely done in resource-limited settings due to cost constraints. For important ant-TB drugs like isoniazid and rifampicin, peak plasma concentration of 3 to 6 mg/L and > 8 mg/L are desired, respectively
^
17
^.

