### Participants on anti-tuberculosis treatment

The current tuberculosis (TB) treatment involves fixed dose combinations based on weight bands, including an intensive phase of rifampicin, isoniazid, ethambutol, and pyrazinamide (RHEZ) for 2 months, followed by a continuation phase of isoniazid and rifampicin (HR) for 4 months. Dosing is determined by weight bands, with 3, 4, or 5 tablets of RHZE or HR depending on weight (<55, 55–69, ≥70 respectively). Each tablet contains 150 mg of rifampicin and 75 mg of isoniazid for both combinations. Fixed dose combinations in the intensive phase include concomitant pyrazinamide and ethambutol.

Serum rifampicin and isoniazid concentrations (C2hr, C4hr, C6hr) will be measured in participants when fasting, and following directly observed therapy, after two weeks of treatment (First TDM). Results of blood concentrations will be received within 24–48 hours and assessed to determine if the C
_max_ and AUC is within the therapeutic targets. Sub-therapeutic C
_max_ concentrations are considered less than 8mg/L and 3mg/L for rifampicin and isoniazid, respectively. AUCs for rifampicin and Isoniazid will also be considered and compared with existing published therapeutic ranges
^
22
^. Participants found to have subtherapeutic drug exposures will have dose escalation and be asked to take one additional pill of the drug that did not achieve therapeutic target concentrations (rifampicin, isoniazid or both) (
Table 3). A second blood draw for measurement of drug concentrations will be performed after another two weeks (Second TDM) and dose adjustment performed again based on the guidance in
Table 3, if concentrations are still below the target. (
Figure 1)

**Table 3. T3:** Dose adjustment table for isoniazid and rifampicin in patients with HIV.

Weight band	Normal drug levels	Sub-target INH <3mg/dl Normal RIF	Normal INH Sub-target RIF <8mg/dl	Sub-target INH <3mg/dl and Sub-target RIF <8mg/dl
<55kg	Continue INH 225 mg and RIF 450 mg (3 FDCs)	Give an additional INH tablet equivalent to: INH 300 mg	Give an additional rifampicin tablet equivalent to 600 mg dose	Give additional rifampicin and isoniazid tablets or FDCs equivalent to 300 mg INH and 600 mg rifampicin

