55–69kg	Continue INH 300 mg and RIF 600 mg (4 FDCs)	Give an additional INH tablet equivalent to INH 375 mg dose	Give an equivalent rifampicin tablet equivalent to 750 mg dose	Give additional rifampicin and isoniazid tablets or FDCs equivalent to 375 mg INH and 750 mg rifampicin
≥70kg	Continue INH 375 mg and RIF 750 mg (5 FDCs)	Give an additional INH tablet equivalent to 450 mg dose	Give an additional rifampicin tablet equivalent to 900 mg dose	Give additional rifampicin and isoniazid tablets or FDCs equivalent to 450 mg INH and 900 mg rifampicin

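### Table 3 prints the isoniazid and rifampicin cut-offs in mg/dl, ten times the mg/L cut-offs that the text sets for dose escalation

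*Protocol article*

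**What the plan says.** All of the relevant text is in the protocol article.

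- **Definition in the text** (Participants on anti-tuberculosis treatment): sub-therapeutic peak "concentrations are considered less than 8mg/L and 3mg/L for rifampicin and isoniazid, respectively".
- **Targets in the Introduction**, for isoniazid and rifampicin in that order: "peak plasma concentration of 3 to 6 mg/L and > 8 mg/L are desired, respectively".
- **Table 3, the three sub-target headers**: "Sub-target INH <3mg/dl Normal RIF"; "Normal INH Sub-target RIF <8mg/dl"; and "Sub-target INH <3mg/dl and Sub-target RIF <8mg/dl". The remaining column, for normal drug levels, carries no cut-off.
- **Role of Table 3**: the text cites it for the one-tablet escalation after the first TDM. It cites it again after the second TDM, with "dose adjustment performed again based on the guidance in" that table for participants still below target.

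**The concern.** The same two numerals appear with two units that differ by a factor of ten, and the larger unit stands in the table that staff would consult to set a dose. The text says results come back within 24 to 48 hours and lead directly to a dose change, so the cut-off is an operating instruction.

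The error runs in one direction. Taken at face value, the table raises the dose of participants who have already reached the target. The protocol treats escalation as carrying risk: it provides adverse event reporting and trial insurance for those whose dose is adjusted, and a monitoring board that can recommend stopping TDM. The cut-off also decides who counts as dose-adjusted. The planned tuberculosis analyses use that grouping, both for target attainment after adjustment and for the exploratory comparison of time to culture negativity.

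**Working it through.** **Inputs**

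- Text cut-offs (Participants on anti-tuberculosis treatment): isoniazid 3 mg/L, rifampicin 8 mg/L.
- Desired peaks (Introduction): isoniazid 3 to 6 mg/L, rifampicin above 8 mg/L.
- Table 3 header cut-offs: isoniazid 3 mg/dl, rifampicin 8 mg/dl.
- Table 3 doses by weight band, before and after one step.

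**Step 1. Convert the header cut-offs.** 1 dl = 0.1 L, so x mg/dl = 10x mg/L.

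- Isoniazid: 3 mg/dl = 30 mg/L, and 30 / 3 = 10 times the text cut-off.
- Rifampicin: 8 mg/dl = 80 mg/L, and 80 / 8 = 10 times the text cut-off.

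**Step 2. Find where the two readings part.**

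| Drug | Sub-target under both | Text: on target; table: sub-target | Not sub-target under either |
|---|---|---|---|
| Isoniazid | below 3 mg/L | 3 to below 30 mg/L | 30 mg/L and above |
| Rifampicin | below 8 mg/L | 8 to below 80 mg/L | 80 mg/L and above |

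Two examples from the middle column:

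- Isoniazid 4 mg/L = 0.4 mg/dl, which is below 3 mg/dl.
- Rifampicin 10 mg/L = 1.0 mg/dl, which is below 8 mg/dl.

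Both are on target by the text and sub-target by the table.

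**Step 3. Compare with the protocol's own isoniazid range.** 3 to 6 mg/L = 0.3 to 0.6 mg/dl, so the whole desired range lies under the 3 mg/dl header. The literal cut-off is 30 / 6 = 5 times the top of that range.

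**Step 4. Size of the escalation step in Table 3** (new dose / old dose − 1).

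| Weight band | Isoniazid | Rifampicin | Increase |
|---|---|---|---|
| <55 kg | 225 to 300 mg | 450 to 600 mg | +33.3% |
| 55–69 kg | 300 to 375 mg | 600 to 750 mg | +25% |
| ≥70 kg | 375 to 450 mg | 750 to 900 mg | +20% |

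**Step 5. Apply the correction.** With mg/L in the headers, they read isoniazid <3 mg/L and rifampicin <8 mg/L. These match the text cut-offs exactly and fit the Introduction's targets.

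**The case against.** The case for treating this as minor is reasonable.

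- **The text already gives the rule.** It defines sub-therapeutic in mg/L shortly before it calls for escalation, and it limits the second adjustment to participants still below target. On that view Table 3 mainly says which tablet to add in each weight band.
- **The literal reading is implausible.** It would class the whole desired isoniazid range as too low, and the article writes its other concentration targets in mg/L. Nothing in the article shows that anyone has used the larger cut-offs.
- **Few participants may be exposed at the first TDM.** The Statistical analysis section reports that 78% (rifampicin) and 84% (isoniazid) of participants in the SOUTH dataset were below target without dose adjustment. Suppose that the same cut-offs and a similar population apply, and that the 25 in the Sample size section is the anti-tuberculosis group. Then 22% × 25 = 5.5 participants for rifampicin and 16% × 25 = 4 for isoniazid would be on target and open to misclassification. The share could rise at the second TDM, after some doses have gone up.
- **There are safeguards.** Adverse events are assessed in those adjusted, the monitoring board reviews toxicity, and any step after the second TDM is discretionary.

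Most of this stands as an account of practical risk: this is very probably a slip, and a careful clinician would probably notice it. It does not make the table right. A dosing table can be copied and used apart from its surrounding text, and the safeguards act only after the dose has been raised. The count of four to six per drug rests on assumptions that the article does not confirm. Figure 1, which shows the procedure, is not available here, so the conclusion does not rely on it.

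**Conclusion.** The contradiction is real and should be corrected before Table 3 is used further. All three sub-target headers state cut-offs ten times those in the text: 30 against 3 mg/L for isoniazid and 80 against 8 mg/L for rifampicin. The Introduction supports the text, so the table is the part in error.

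The harm is conditional on someone applying the headers as printed. If they do, a participant already on target receives a step of +20% to +33% in that drug. Management of participants below 3 or 8 mg/L does not change. The article does not allow a firm count of those affected or an estimate of the effect on target attainment.

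The point ranks high because of where the error sits, in the table cited for escalation at both TDM rounds, and because the correction costs so little. The abstract says that enrolment began in September 2024, so participants may already have been dosed from this table.

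**What to change.** Replace mg/dl with mg/L in all three sub-target headers of Table 3, so that they read isoniazid <3 mg/L and rifampicin <8 mg/L. Confirm that the laboratory reports concentrations in mg/L and that any working copy of the table at the clinic uses the same unit. Send the study team a short notice of the correction. As enrolment has begun, it would be sensible to check that dose changes already made used the mg/L cut-offs.

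The cost is a unit correction in three column headers and one notice. The design, sample size and analysis stay as they are.

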**Figure 1. f1:**
[figure not shown]
Therapeutic drug monitoring procedure with dose adjustment for participants on TB drugs.

If the participant is still not achieving the therapeutic target concentrations after the second C
_max_, another 1hr and 6hr blood draw will be conducted to assess for the presence of fast or delayed absorption. An additional dose adjustment with 1 additional tablet of the respective drug may be prescribed for these patients at the discretion of the study team and with consideration of observed side effects, treatment response, and concentrations attained. Those who attain therapeutic drug concentrations during TDM will revert to the previous dose. The final doses provided will be recorded for all participants.

**
*Sputum analysis*
**

For participants with tuberculosis, sputum cultures will be conducted at the Makerere University Microbacteriology laboratory. Cultures using Mycobacterium Growth Indicator tube (MGIT) and Lowenstein-Jensen (LJ) agar will be conducted within 7 days of enrolment and will be conducted every two weeks for the first eight weeks of TB treatment (intensive phase).

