**Primary endpoints**

Pharmacokinetic parameters

Trough concentrations (Ctrough) for amoxicillin, ciprofloxacin, azithromycin and ceftriaxone

Pharmacodynamic parameters

Clinical response to antibiotics through the time of treatment will be assessed. Clinical response is either clinical cure (resolution of symptoms) or clinical failure (lack of improvement in signs and symptoms of infection OR recurrence of signs/symptoms of infection after initial improvement.

**
*On TB treatment*
**

Pharmacokinetic parameters

Maximum concentrations (Cmax) and area under the concentration-time curve (AUC) defined as the total exposure for rifampicin, isoniazid

Pharmacodynamic parameters

1. Clinical response will be assessed according to the World Health Organization definitions of cure, completed and treatment failure, which will be extracted from the clinic database.2. Occurrence of adverse drug reactions

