### Statistical analysis

**
*Analysis of data on antimicrobial drugs: sparse pharmacokinetic data*
**

Sparse pharmacokinetic data for antimicrobials will be analysed as medians with standard deviations. We assess for the effect of covariates like age, sex, body-mass index, CD4 cell counts on drug concentrations

**
*Analysis of data on antimicrobial drugs: intensive pharmacokinetic data*
**

Non-linear mixed-effects models will be used to calculate the pharmacokinetic parameters of the drugs and this will include the maximum plasma concentration (Cmax), time to maximum plasma concentration (Tmax), and area under the plasma concentration-time curve (AUC). We will also explore the effects of covariates like age, sex, concomitant medications, and body-mass index on the pharmacokinetic parameters.

**
*Pharmacodynamic parameters*
**

We will use pharmacokinetic and pharmacodynamic models to assess the effect of the pharmacokinetic parameters on clinical response. For sparse pharmacokinetic data, we will use drug concentrations as a covariate in the linear regression models predicting clinical response. Clinical response will be defined as either clinical cure (resolution of symptoms) or clinical failure (lack of improvement in signs and symptoms of infection or recurrence of signs/symptoms of infection after initial improvement or death considered at least possibly due to the infection.

**
*Analysis of data on anti-tuberculosis drugs*
**

For participants on anti-tuberculosis drugs, we will evaluate whether dose adjustment leads to the achievement of therapeutic targets.

As an exploratory objective, using Kaplan Meier survival analysis, time to sputum culture negativity will be compared for those who received dose adjustment and those who did not receive dose adjustment within this study. We will also utilize the SOUTH dataset where drug concentrations of rifampicin and isoniazid were measured (without dose adjustment), where 78% and 84% of participants had rifampicin and isoniazid concentrations below the therapeutic targets respectively.

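### The reversion sentence in the TB dose-adjustment procedure, read literally, moves participants who reached target back to a dose that measured below target, with no later scheduled PK draw

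*Protocol article*

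**What the plan says.** The procedure is in the protocol article under 'Participants on anti-tuberculosis treatment', Table 3 and the text after Figure 1.

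- **First TDM, after two weeks of treatment.** "Participants found to have subtherapeutic drug exposures will have dose escalation and be asked to take one additional pill" of the drug that missed its target. The Cmax thresholds are 8 mg/L for rifampicin and 3 mg/L for isoniazid, and AUC is also considered. Participants with normal levels keep their dose; the Table 3 entry for the lowest weight band is "Continue INH 225 mg and RIF 450 mg (3 FDCs").
- **Second TDM, two weeks later.** The dose is adjusted again only where concentrations remain under target.
- **Still low after the second TDM.** For these participants "another 1hr and 6hr blood draw will be conducted to assess for the presence of fast or delayed absorption", and one more tablet may be given at the study team's discretion.
- **Closing rule of that paragraph.** "Those who attain therapeutic drug concentrations during TDM will revert to the previous dose". It does not say which participants, at what time, or which earlier dose.

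Table 1 marks TB PK draws at weeks 2 and 4 and none at weeks 6 or 8. The Statistical analysis section says "we will evaluate whether dose adjustment leads to the achievement of therapeutic targets". As an exploratory objective, "time to sputum culture negativity will be compared for those who received dose adjustment" and those who did not.

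**The concern.** TDM with dose adjustment is meant to find a dose that reaches target and use it. Read literally, the closing rule takes the extra tablet away from the participants in whom it worked, while those still below target may keep or gain tablets. Staff following the text would lower an effective dose, and no planned sample would show the result.

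Two things are at stake. One is the exposure that attainers have for the rest of treatment. The other is the meaning of the adjusted group in the culture comparison, which would include people who held the higher dose only briefly.

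**Working it through.** **1. On whom the sentence can act.** There are three routes through the procedure.

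| Route | Dose before attaining target | 'Previous dose' | How that dose measured |
|---|---|---|---|
| On target at first TDM | Standard, unchanged | None; Table 3 says continue | Not applicable |
| On target after one added tablet | First escalated dose | Standard weight-band dose | Below target at first TDM |
| On target after a second added tablet | Second escalated dose | First escalated dose | Below target at second TDM |

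Only the last two rows have a dose to go back to. In both, the participant had already measured below target on that dose.

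**2. Size of the cut after one step.** Inputs are the Table 3 totals. Formula: 1 − standard dose / escalated dose.

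| Weight band | Rifampicin (mg) | Isoniazid (mg) | Cut |
|---|---|---|---|
| <55 kg | 600 to 450: 1 − 450/600 | 300 to 225: 1 − 225/300 | 25.0% |
| 55–69 kg | 750 to 600: 1 − 600/750 | 375 to 300: 1 − 300/375 | 20.0% |
| ≥70 kg | 900 to 750: 1 − 750/900 | 450 to 375: 1 − 375/450 | 16.7% |

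The cut applies to whichever drug was escalated, or to both. Table 3 does not print totals for a second step, so no percentage is given for two-step attainers.

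**3. Whether a later sample would show a fall.** Table 1 has nothing for TB participants after week 4. The extra 1-hour and 6-hour draw is reserved for those still below target, so a participant who attains target at week 4 and then reverts has no planned draw on the resumed dose.

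**4. Consistency with the second-TDM rule.** The main text makes adjustment at the second TDM conditional on still being below target. That implies no change for someone on target at week 4. The closing rule changes the dose of that same participant, so the two statements pull against each other.

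**5. Time on the adjusted dose, one-step attainers.** The protocol gives no date for reversion. Assume that it happens at about week 4, when the second TDM is read.

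- Adjusted dose held from week 2 to week 4: 4 − 2 = 2 weeks.
- Share of the eight weeks of culture follow-up: 2/8 = 25%.
- Cultures after the first adjustment fall at weeks 4, 6 and 8. Two of the three (weeks 6 and 8) come after reversion.
- The intensive phase is 2 months, "followed by a continuation phase of isoniazid and rifampicin (HR) for 4 months", so treatment lasts 6 months, or about 26 weeks: 2/26 = 7.7%.

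For these participants the treatment outcome ("Clinical response will be assessed according to the World Health Organization definitions of cure, completed and treatment failure") would mostly follow standard dosing. That does not extend to two-step attainers, whose resumed dose is still above standard.

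**The case against.** The strongest reply is that the intent is unresolved. The sentence closes a paragraph about participants still low at the second TDM, directly after the absorption draw. Stepping back makes sense there if that draw shows that the regular samples missed a peak. The authors may also have meant only that attainers carry on with the dose they were taking. Figure 1, which sets out the procedure, is not shown. This stands as a reason for caution: the documents do not establish a plan to de-escalate every responder. It does not rescue the wording, which covers anyone attaining target during TDM and is not confined to the extra draw.

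The consequences are also limited. Reverted one-step participants receive the standard weight-band dose. The culture comparison is exploratory, and final doses are recorded. All of this stands. However, the final dose alone would not separate a reverted one-step attainer from someone never escalated.

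Three stronger readings are tempting, and the documents do not support them:

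- **That reversion leaves participants under-dosed relative to usual care.** It does not. It returns them to the standard dose or, after two steps, to a dose above it.
- **That objective 2 can no longer be assessed.** It can, because week-4 attainment is read before any reversion.
- **That a second-TDM Cmax limit shows who would fall below target.** If Cmax is proportional to dose, the rifampicin limit for <55 kg is 8 × 600/450 = 10.67 mg/L. Under the same assumption, anyone escalated for a Cmax under 8 mg/L on 450 mg must be under 10.67 mg/L on 600 mg. The limit separates nobody and only restates the week-2 result.

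**Conclusion.** The point holds in a limited form. The sentence as worded acts only on escalated participants and returns them to a dose that measured below target. It conflicts with the conditional rule at the second TDM, and no TB PK draw is scheduled afterwards.

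The cut is 25%, 20% or 16.7% by weight band for one-step attainers, directly from Table 3. The figure of about 2 of 8 culture weeks rests on the assumption that reversion happens at about week 4. No number of affected participants can be given, because the documents state no response rate to one extra tablet.

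Sustained exposure after week 4 and the exploratory culture comparison are affected; week-4 attainment is not. Confidence is moderate, because a narrower intent is possible and Figure 1 is not shown. The sentence should be corrected under either intent.

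**What to change.** Replace the sentence with: *Participants who reach target continue the dose at which target was reached, unless toxicity requires reduction.* If reversion is meant only for participants whose extra 1-hour and 6-hour draw shows a missed peak, limit the sentence to them.

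The edit is one sentence, but it changes a dosing rule after enrolment began in September 2024. It therefore needs a protocol amendment with ethics approval before use.

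The first option also keeps attainers above the standard weight-band dose for longer, up to about 26 − 4 = 22 further weeks for someone on target at week 4. Table 1 marks ALT and bilirubin for TB participants only at week 2, so later safety would rest on the existing adverse event reporting, standard-of-care testing and Data Monitoring Board review. The sponsor should confirm with the Board that this is enough. Neither option requires a new PK visit or a new analysis.

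### Read literally, the TB dosing text sends a participant who reaches target on a raised dose back to the dose that measured sub-target, in conflict with the second-TDM rule

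*Protocol article*

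**What the plan says.** All of this is in the Protocol article, under 'Participants on anti-tuberculosis treatment' unless stated.

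- First TDM, after two weeks on the weight-band dose: "Participants found to have subtherapeutic drug exposures will have dose escalation", by one extra tablet of whichever drug is low. The peak thresholds are 8 mg/L for rifampicin and 3 mg/L for isoniazid.
- Second TDM, two weeks later: the dose is adjusted again by Table 3 "if concentrations are still below the target".
- Table 3: the column for normal levels lists weight-band doses only, for example "Continue INH 225 mg and RIF 450 mg (3 FDCs" below 55 kg. The sub-target columns list the raised doses, for example "Give an additional rifampicin tablet equivalent to 600 mg dose" below 55 kg and "Give an additional rifampicin tablet equivalent to 900 mg dose" at 70 kg or more.
- After Figure 1, for those still low after the second TDM: "another 1hr and 6hr blood draw will be conducted to assess for the presence of fast or delayed absorption", and one further tablet is possible at the study team's discretion.
- The same paragraph then states, with no limit on whom it covers: "Those who attain therapeutic drug concentrations during TDM will revert to the previous dose". It ends: "The final doses provided will be recorded for all participants".
- Table 1 ('Study design') marks PK draws at day 2, week 2 and week 4, and ALT and bilirubin at week 2 only.

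**The concern.** Only participants measured below target are escalated. For someone escalated once, the only previous dose is the weight-band dose on which the low level was found. Someone at target at week 2 never changed dose and has nothing to revert to. Followed as written, the sentence therefore withdraws the raised dose because it worked, and no draw is scheduled to show what happens next.

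Three things are at stake:

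- The exposure of these participants for the rest of treatment.
- The reach of the attainment result. It would describe about two weeks on the raised dose, whereas the Discussion wants the findings to inform rifampicin and isoniazid dosing in practice.
- Secondarily, the exploratory comparison of time to culture negativity. Its dose-adjusted group could mix people who reverted with people still on a raised dose.

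Enrolment began in September 2024 (Abstract, Results), so the rule may already be in use.

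**Working it through.** There is no plan figure to reproduce, because this is a dosing rule. The check traces the rule and then sizes the step back.

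**Tracing a week-4 responder**

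1. Week 2: level below target on the weight-band dose, so one tablet is added.
2. Week 4: level at target on the raised dose.
3. The second-TDM rule acts only on those still low, which suggests no change.
4. Table 3 has no entry for staying on a raised dose. Its normal-levels column says to continue but prints only weight-band doses.
5. The sentence after Figure 1 says to revert. The section uses the label TDM for the week-2 and week-4 measurements, so a week-4 responder falls within its wording.
6. The 1 h and 6 h draw is for those still low, and Table 1 has no PK draw after week 4. No scheduled level follows a reversion.

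Steps 3 and 5 give different instructions for the same participant.

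**Size of the step back** (doses from Table 3; step back = 1 − weight-band dose / raised dose)

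| Weight band | Rifampicin, raised to weight-band | Isoniazid, raised to weight-band | Step back |
|---|---|---|---|
| <55 kg | 600 to 450 mg | 300 to 225 mg | 1 − 450/600 = 1 − 225/300 = 25% |
| 55–69 kg | 750 to 600 mg | 375 to 300 mg | 1 − 600/750 = 1 − 300/375 = 20% |
| ≥70 kg | 900 to 750 mg | 450 to 375 mg | 1 − 750/900 = 1 − 375/450 = 16.7% |

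**Duration.** Treatment is 2 + 4 months, about 26 weeks. The raised dose would cover roughly weeks 2 to 4: 2/26 = 8% of treatment, and 2/8 = 25% of the eight weeks of culture follow-up. The time after reversion is 26 − 4 = 22 weeks, and 22/26 = 85%.

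**Illustration of levels (assumption).** The document gives no dose–peak relation. Assume that the peak is proportional to dose^g, with g = 1 and a range of 0.8 to 1.5. A participant exactly at target on the raised dose would, on reverting, have these peaks (<55 / 55–69 / ≥70 kg):

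- Rifampicin, target 8 mg/L, g = 1: 8 × 450/600 = 6.0; 8 × 600/750 = 6.4; 8 × 750/900 = 6.67. With g = 0.8: 6.36 / 6.69 / 6.91. With g = 1.5: 5.20 / 5.72 / 6.09.
- Isoniazid, target 3 mg/L, g = 1: 3 × 225/300 = 2.25; 3 × 300/375 = 2.4; 3 × 375/450 = 2.5. With g = 0.8: 2.38 / 2.51 / 2.59. With g = 1.5: 1.95 / 2.15 / 2.28.

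All are below target. To stay at target after reverting (g = 1), the peak on the raised dose would have to be at least 10.67 / 10.0 / 9.6 mg/L for rifampicin or 4.0 / 3.75 / 3.6 mg/L for isoniazid.

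**The case against.** **Figure 1 is not shown.** It is the decision flow for this very step and may keep responders on the raised dose. That stands as a limit on certainty. It does not make the unqualified sentence right: a figure that said otherwise would leave text and figure in conflict.

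**The sentence may be narrower than it looks.** It closes the paragraph on the absorption draw, so it may be meant only for people whose peak had been missed, who would then drop a tablet added since. That reading is open. If it is correct, though, the text has no explicit rule for the ordinary success case of being at target at week 4, beyond what the second-TDM rule implies.

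**Other text points towards no change.** The second-TDM condition does so, and Table 3 uses the word continue. This is fair, and it is why the point is a conflict in the text. A reader might infer that the sponsor deliberately chose to de-escalate responders. The document does not settle that intent.

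**Table 1 may not list every draw.** The 1 h and 6 h draw has no entry of its own there, and the article condenses a fuller protocol. The claim is therefore limited to what Table 1 and the text schedule.

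**The analytic effect is small.** This stands. A reader might infer that the target-attainment result is compromised, but it is measured at week 4, before any reversion. The culture comparison is labelled exploratory, grouping by whether the dose was ever adjusted is coherent, and a split by recorded final dose can be left to an analysis plan.

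**The number affected is unknown.** This also stands. The sub-target proportions quoted from the SOUTH dataset (78% rifampicin, 84% isoniazid) come from a study without dose adjustment. They do not show how many escalated participants would reach target at week 4.

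**Conclusion.** The point holds as a conflict in a stated treatment rule. One sentence, read literally, returns week-4 responders to the dose that measured sub-target; the second-TDM rule suggests leaving them where they are. It should be fixed. Confidence is medium, because Figure 1 is unseen and a narrower intent is possible.

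The step back of 25%, 20% or 16.7% is exact from Table 3. The durations (2 and 22 of about 26 weeks) assume reversion at week 4 with no later clinical change of dose. The peak levels rest on the assumed dose relation and apply to someone only just at target. It would go too far to say that every reverted participant becomes sub-target: those with enough margin would stay at target, but no scheduled draw would identify them.

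**What to change.** Replace the sentence with:

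> Escalated participants who attain target continue the dose on which target was attained, subject to tolerability and clinical judgement; if the 1 h/6 h draw shows that target was in fact attained on the dose being taken at that draw, that dose is kept and any tablet added after it is withdrawn.

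The second clause refers to the dose being taken at the draw because participants who were escalated and remain low are by then on a raised dose. The draw cannot show attainment on the original weight-band dose.

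Align Table 3 and Figure 1 with this, including an entry for staying on a raised dose. If general reversion is truly intended, state that the attainment result applies only to the escalated period.

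Cost: wording changes that need ethics approval before use ('Ethics and consent'), with no added participants or PK draws. If general reversion is the current rule, the change also means up to about 22 more weeks on a one-tablet-higher dose. The existing adverse-event reporting for dose-adjusted participants ('Safety assessment') and the review by the Data Monitoring Board would cover that time. Because Table 1 schedules ALT and bilirubin only at week 2, before any raised dose, later liver tests would rest on standard of care.
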